| PPD (Mantoux test)                      | X                                                                                         |                            |                                |                                |                            |                            |                                         |                           |                            |                            |                             |                             |                                 |                                 |                                 |                                          |
| Chest X-ray                             | X                                                                                         |                            |                                |                                |                            |                            |                                         |                           |                            |                            |                             |                             |                                 |                                 |                                 |                                          |
| ECG                                                 | X                                                                                         |                            |                                |                                |                            |                            |                                         |                           |                            |                            |                             |                             |                                 |                                 |                                 | X                                        |
| RNA Analysis                                        |                                                                                           | X                          |                                |                                |                            |                            |                                         |                           | X                          |                            |                             |                             |                                 |                                 |                                 | X                                        |
| Study treatment
administration                   |                                                                                           | X                          |                                |                                | X                          | X                          |                                         | X                         | X                          | X                          | X                           | X                           |                                 |                                 |                                 |                                          |
| Monitoring of adverse events                        | <----- MONITOR AND RECORD THROUGHOUT THE STUDY AS PER INSTRUCTIONS IN SECTION 15.2 -----> |                            |                                |                                |                            |                            |                                         |                           |                            |                            |                             |                             |                                 |                                 |                                 |                                          |
| Monitoring of concomitant
therapy                | <----- MONITOR AND RECORD THROUGHOUT THE STUDY AS PER INSTRUCTIONS IN SECTION 15.2 -----> |                            |                                |                                |                            |                            |                                         |                           |                            |                            |                             |                             |                                 |                                 |                                 |                                          |

CONFIDENTIAL

The information contained herein may not be used, disclosed, or published without the written consent of  
Biogen Idec Inc.

| Tests and Evaluations                     | Visit 10
Wk 18
(± 3 d)                                       | Visit 11
Wk 22
(± 3 d) | Visit 12
Wk 26e
(± 3 d) |
|--------------------------------------------------|-----------------------------------------------------------------------------|---------------------------------------|---------------------------------------------------|
| Medical history                                  |                                                                             |                                       |                                                   |
| Physical examination                             |                                                                             |                                       | X                                                 |
| Vital signs                          | X                                                                           | X                                     | X                                                 |
| ACR Core Set measurements            | X                                                                           | X                                     | X                                                 |
| QoL (SF-36 / FACIT-F)                            |                                                                             |                                       | X                                                 |
| Sjogrens assessments                 |                                                                             |                                       | X                                                 |
| hsCRP, ESR                           | X                                                                           | X                                     | X                                                 |
| RF/ anti-CCP-2                                   |                                                                             |                                       |                                                   |
| RA disease markers  / Cytokine panel |                                                                             |                                       |                                                   |
| Quantitative FACS analysis           |                                                                             |                                       |                                                   |
| Serum BG9924 PK                                  |                                                                             | X                                     | X                                                 |
| Hematology                                       |                                                                             |                                       | X                                                 |
| Quantitative Ig                                  |                                                                             |                                       | X                                                 |
| Blood chemistry                                  |                                                                             |                                       | X                                                 |
| INR, PT, and aPTT                                |                                                                             |                                       | X                                                 |
| Hep C, Hep B test                                |                                                                             |                                       |                                                   |
| ANA / anti-dsDNA antibody assays                 |                                                                             |                                       | X                                     |
| Serum anti-BG9924 antibody assay                 |                                                                             |                                       | X                                                 |
| Tetanus antibody titers                          |                                                                             |                                       | X                                                 |
| Serum pregnancy test                             |                                                                             |                                       |                                                   |
| Urinalysis                                       |                                                                             |                                       | X                                                 |
| Urine pregnancy test                             |                                                                             |                                       |                                                   |
| PPD (Mantoux test)                   |                                                                             |                                       |                                                   |
| Chest X-ray                          |                                                                             |                                       |                                                   |
| ECG                                              |                                                                             |                                       |                                                   |
| RNA Analysis                                     |                                                                             |                                       |                                                   |
| Study treatment administration                   |                                                                             |                                       |                                                   |
| Monitoring of adverse events                     | MONITOR AND RECORD THROUGHOUT THE STUDY AS PER INSTRUCTIONS IN SECTION 15.2 |                                       |                                                   |
| Monitoring of concomitant therapy                | MONITOR AND RECORD THROUGHOUT THE STUDY AS PER INSTRUCTIONS IN SECTION 15.2 |                                       |                                                   |

CONFIDENTIAL

The information contained herein may not be used, disclosed, or published without the written consent of Biogen Idec Inc.

Vital signs include temperature, heart rate, respiratory rate, and blood pressure. Blood pressure to be performed supine after 5 minutes rest.

Measurements include: swollen and tender joint counts (66/68), subject/Investigator global assessment of disease activity, HAQ-DI, and subject's assessment of pain (VAS)

Assessments include: subject-reported dryness including VAS (ocular, vaginal, skin, and oral) and OSDI. To be conducted in subjects with Sjogrens syndrome only.

ESR to be performed at local laboratory.

RA disease markers include: serum BAFF, COMP, calgranulin, and MMP3.

**Only to be taken from subjects participating in the optional PK sub-study.**

PPD test to be read 48-72 hours after planting.

Not required if performed within 3 months prior to Day 0 and was without clinically significant abnormality. However, if PPD induration is  $\geq 5$  mm, but  $< 10$  mm (size of raised bump, not redness), a chest X-ray is required, regardless of when the last X-ray was taken.

Only to be taken from subjects with positive ANA/anti-dsDNA at Week 14.

a**Visit only applicable to subjects participating in the optional PK sub-study. Subjects will sign a separate informed consent form.**

bOption to enter safety data extension study. If subject withdraws from the study prior to Visit 9/Week 14, all Week 14 assessments should be completed at the withdrawal visit.

cIf subject withdraws from the study during the post-treatment period, Week 26 assessments should be completed at the withdrawal visit.

---

CONFIDENTIAL

The information contained herein may not be used, disclosed, or published without the written consent of  
Biogen Idec Inc.

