| Serum pregnancy test                                | X                                                                                         |                            |                                |                                |                            |                            |                                         |                           |                            |                            |                             |                             |                                 |                                 |                                 |                                          |
| Urinalysis                                          | X                                                                                         | X                          |                                |                                |                            |                            |                                         |                           |                            |                            |                             |                             |                                 |                                 |                                 | X                                        |
| Urine pregnancy test                                |                                                                                           | X                          |                                |                                |                            |                            |                                         |                           |                            |                            |                             |                             |                                 |                                 |                                 | X                                        |

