#### MISCELLANEOUS

21. Nursing mothers, pregnant women, or women who are planning to become pregnant while in the study.
22. Male and female subjects of childbearing potential not willing to practice effective birth control for the duration of the study. Female subjects must be:  
(1) postmenopausal for at least 12 months, (2) surgically sterile, or (3) willing to use 2 documented forms of birth control (e.g., barrier and spermicide, intrauterine device and barrier or spermicide, or birth control pill and barrier or spermicide).
23. Blood donation (1 unit or more) within 1 month prior to Screening.
24. History of drug or alcohol abuse (as determined by the Investigator) within the 1 year prior to Day 0.
25. Current enrollment in any other investigational drug study.
26. Previous participation in this study.

---

CONFIDENTIAL

The information contained herein may not be used, disclosed, or published without the written consent of  
Biogen Idec Inc.

27. Subjects who are expected to be unavailable for the duration of the trial, likely to be noncompliant with the protocol, or who are felt to be unsuitable by the Investigator/Sponsor for any other reason.

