## 11 TREATMENT

### 11.1 Treatment Schedule

Subjects will receive BG9924 or placebo via SC injection by a healthcare provider at the study site every other week for 12 weeks. All subjects will receive a loading dose as described below. Subjects will be randomized to one of the following dose groups:

- Placebo every other week (loading dose at Weeks 0 and 1)
- BG9924 5 mg every other week (loading dose of 3 mg at Weeks 0 and 1)
- BG9924 70 mg every other week (loading dose of 40 mg at Weeks 0 and 1)
- BG9924 200 mg every other week (loading dose of 120 mg at Weeks 0 and 1)
- BG9924 70 mg monthly (alternates with placebo every other visit, loading dose of 40 mg at Weeks 0 and 2)
- BG9924 200 mg monthly (alternates with placebo every other visit, loading dose of 120 mg at Weeks 0 and 2)

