### 11.2 Removal of Subjects from Treatment and/or Study

#### 11.2.1 Discontinuation of Treatment

Unless otherwise indicated, a subject *must* permanently discontinue BG9924 for any of the following reasons:

- Occurrence of severe (in the opinion of the Investigator) local injection site reaction or hypersensitivity reaction.
- Occurrence of any clinically significant (in the opinion of the Investigator) opportunistic infection or other serious infection.
- Occurrence of any non-cutaneous malignancies or melanoma.
- The subject becomes pregnant. Treatment must be discontinued *immediately*. Report the pregnancy according to the instructions in Section 15.5.2.
- The subject desires to discontinue study treatment under this protocol.
- The subject experiences a medical emergency that necessitates permanent discontinuation of treatment.
- The subject experiences a medical emergency that necessitates unblinding of the subject's treatment assignment.
- The Investigator determines discontinuing the study treatment is in the best interest of the subject.

Subjects who prematurely discontinue treatment will be permanently withdrawn from treatment, and every effort must be made to encourage them to complete all follow-up

visits from Visit 9/Week 14 to Visit 12/Week 26. Subjects who prematurely discontinue may possibly be replaced in the accrual scheme. The reason(s) for discontinuation of the study treatment must be recorded in the subject's CRF.

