#### 15.5.2 Pregnancy

If a female subject becomes pregnant, study treatment must be discontinued *immediately*.

The Investigator must report the pregnancy by faxing the appropriate form to [REDACTED] within 24 hours of the study site staff becoming aware of the [REDACTED]

CONFIDENTIAL

The information contained herein may not be used, disclosed, or published without the written consent of  
Biogen Idec Inc.

pregnancy, [REDACTED]  
[REDACTED] The Investigator or study site staff must report the outcome of the pregnancy to [REDACTED]

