### 15.6 Investigator Responsibilities

The Investigator's responsibilities include the following:

- Monitor and record all AEs, which includes SAEs, regardless of the severity or relationship to study treatment.
- Determine the seriousness, relationship, and severity of each event.
- Determine the onset and resolution dates of each event.
- Monitor and record all pregnancies and follow-up on the outcome of the pregnancy and status of the infant.

- Complete an SAE form for each SAE and fax it to [REDACTED] within 24 hours of the study site staff becoming aware of the event.
- Pursue SAE follow-up information actively and persistently. Follow-up information must be reported to [REDACTED] within 24 hours of the study site staff becoming aware of new information.
- Ensure all AE and SAE reports are supported by documentation in the subjects' medical records.
- For sites using a local ethics committee, notify the ethics committee as per ethics committee requirements, of any SAEs. A copy of ethics committee notification must also be sent to your Clinical Monitor in a timely manner.

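### No pregnancy test is scheduled between Day 0 and Day 98, so during dosing the immediate-stop rule relies on self-report, clinical suspicion or an unscheduled test

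*Protocol*

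**What the plan says.** **Testing.** Section 4 and the visit lists in Section 14.2 agree. A serum test is listed at Screening (14.2.1). The row "Urine pregnancy test" is marked at Visit 1, Day 0 (14.2.2) and Visit 9, Day 98 ± 3 (14.2.13) only. The lists for Visits 2 to 8 (14.2.4, 14.2.5, 14.2.7 to 14.2.11) include study treatment and no pregnancy test. The PK sub-study visits have none either.

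**Dosing.** Section 11.1: "Subjects will receive BG9924 or placebo via SC injection by a healthcare provider at the study site every other week for 12 weeks". With the loading dose, injections fall on Days 0, 7, 14, 28, 42, 56, 70 and 84.

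**Stop rule.** Section 11.2.1 lists among the mandatory reasons for permanent discontinuation: "The subject becomes pregnant. Treatment must be discontinued" immediately. Section 15.5.2 repeats it: "If a female subject becomes pregnant, study treatment must be discontinued" immediately. The pregnancy report is due "within 24 hours of the study site staff becoming aware of the" pregnancy.

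**Other safeguards.** Exclusion criterion 21 bars "Nursing mothers, pregnant women, or women who are planning to become pregnant while in the study". Criterion 22 and Section 14.1 require contraception. Section 15.6 tells the investigator to "Monitor and record all pregnancies and follow-up on the outcome of the pregnancy and status of the infant". Under Section 4, footnote b, a subject who withdraws before Week 14 has the Week 14 assessments, and so the urine test, at the withdrawal visit.

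**The concern.** The protocol treats exposure in pregnancy as something to end at once. To act on that, someone has to know that the subject is pregnant. For a subject who stays on treatment, the first scheduled test after Day 0 comes 14 days after the last injection, when nothing is left to stop. The other safeguards either prevent pregnancy (contraception, exclusion of women planning pregnancy) or act once it is already known or suspected (the 24-hour report, investigator discretion, adverse-event monitoring). The duty to monitor for pregnancies comes with no scheduled test during dosing.

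What is at stake is the individual subject and her pregnancy: an unrecognised pregnancy could go on being dosed to Week 12. Earlier repeat-dose experience in RA, as Section 5.2 describes it, is a little over 32 subjects in a study of four weekly doses.

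**Working it through.** **Step 1. The gap as scheduled.** Dosing days strictly between the tests on Day 0 and Day 98 are 7, 14, 28, 42, 56, 70 and 84, which is seven visits. The interval is 98 days, or up to 101 with the ±3-day window. From last dose to next test: 98 − 84 = 14 days.

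**Step 2. Dosing visits after a conception, current plan.** Assume conceptions are spread evenly over Days 0 to 84 and that none is recognised before Day 98. The injection on day *d* follows a conception with probability *d*/84, so the mean number of later dosing visits is

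(7 + 14 + 28 + 42 + 56 + 70 + 84)/84 = 301/84 = 3.58.

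**Step 3. Adding tests on Days 28, 56 and 84, before the injection.** A positive result on those days saves 5, 3 or 1 dosing visits. Assume a test turns positive 14 to 28 days after conception.

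- Lag 28 days: (28×3 + 28×1 + 28×0)/84 = 1.33 visits avoided, leaving 2.25.
- Lag 14 days: (14×5 + 28×3 + 28×1 + 14×0)/84 = 2.17 visits avoided, leaving 1.42.

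As shares of 3.58 these are 37% and 60%. Conceptions in the last 28 or 14 days of dosing gain nothing.

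**Step 4. Allowing for earlier recognition.** Steps 2 and 3 give a ceiling, because women may notice and report a pregnancy. Suppose recognition comes *r* days after conception and dosing then stops. The current-plan mean becomes the sum of min(*d*, *r*) over the seven dosing days, divided by 84.

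| Recognition | Current plan | With tests, lag 28 | With tests, lag 14 | Avoided |
|---|---|---|---|---|
| None | 301/84 = 3.58 | 2.25 | 1.42 | 1.33 to 2.17 |
| 42 days | 217/84 = 2.58 | 2.25 | 1.42 | 0.33 to 1.17 |
| 35 days | 189/84 = 2.25 | 2.08 | 1.42 | 0.17 to 0.83 |
| 28 days | 161/84 = 1.92 | 1.92 | 1.42 | 0.00 to 0.50 |

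**Step 5. Active doses only.** By the 2:2:2:2:1:1 allocation, 0.6 of subjects receive BG9924 every other week, 0.2 monthly and 0.2 placebo. The monthly arms alternate BG9924 with placebo, and the exact weeks are not stated. Assume active doses after Day 0 at Weeks 2, 6 and 10, or at Weeks 2, 4, 8 and 12. With no early recognition, the tests avoid 0.33 or 1.00 active doses in those arms at lag 28, and 0.67 or 1.50 at lag 14. Overall:

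- Lag 28: 0.6×1.33 + 0.2×(0.33 to 1.00) = 0.87 to 1.00.
- Lag 14: 0.6×2.17 + 0.2×(0.67 to 1.50) = 1.43 to 1.60.

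**Step 6. How many conceptions.** The protocol gives neither the number of women of childbearing potential nor a pregnancy rate. Assuming 50 to 150 women and 1% to 6% per year, conceptions during dosing number 50×0.01×84/365 = 0.12 to 150×0.06×84/365 = 2.07.

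**Step 7. What remains after the change.** Test days would be 0, 28, 56, 84 and 98. The longest nominal interval is 28 days, or 59 − 25 = 34 with windows. At a 28-day lag, a conception just after Day 0 is missed on Day 28 and found on Day 56, after injections on Days 7, 14, 28 and 42: four doses.

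**The case against.** The strongest reply is that nothing here is misstated. The table and visit lists agree, any stop rule acts on awareness, and two tests before a 12-week course plus one two weeks after it, with contraception throughout, is a design choice. The documents report no reproductive-toxicity signal for BG9924 and set no required test interval. Contraception is strict: Section 14.1 also binds men and does not exempt vasectomy or tubal ligation. Site staff see each subject every one to two weeks. All of this stands. A reader might infer that the stop rule and the schedule contradict each other; they do not. The rule can be followed as written, but it has no scheduled trigger during dosing.

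The second reply concerns size. The 37% to 60% reduction might be read as the expected benefit. It is a ceiling that assumes nobody recognises a pregnancy before Day 98, and step 4 shows how far it falls. Likewise, under the proposed schedule at most two dosing visits (Weeks 1 and 2) fall strictly between consecutive tests. That does not mean at most two exposed doses, since test lag allows up to four.

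The third reply concerns cost, and it also stands. Section 11.3 says missed doses cannot be made up, and the visit windows are ±3 days, so a false positive not resolved in time loses a dose. Acting on one without confirmation would mean permanent discontinuation under 11.2.1. Serum testing is done centrally (19.1.4) and needs blood. With 50 to 150 women there would be 150 to 450 added tests. At an assumed false-positive rate of 0.1% to 1%, that is 0.15 to 4.5 false positives, comparable in number to the conceptions. A confirmation step is therefore part of the fix.

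None of these replies points to a scheduled test while treatment is still being given.

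**Conclusion.** The point holds as a weakness in the safety schedule. In a subject who completes dosing, seven injection visits pass with no scheduled pregnancy test, and the immediate-stop rule depends on self-report, clinical suspicion or an unscheduled test. No endpoint, power figure or analysis is affected.

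The benefit of adding tests is modest: at most 1.3 to 2.2 of 3.6 later dosing visits avoided per conception, and about 0.0 to 1.2 if pregnancy is recognised at 4 to 6 weeks. These figures assume conceptions spread evenly over Days 0 to 84 and a test lag of 14 to 28 days. The lag, recognition times, numbers of women and pregnancy rates are all assumptions; the counts of visits and days come from the protocol. Few conceptions are expected. The case rests on the consequence for the individual and the low cost of the change, so it is a recommended amendment and not a fault that puts the trial's conclusions in doubt.

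**What to change.** In the Section 4 table and in 14.2.7, 14.2.9 and 14.2.11, add a urine pregnancy test for women of childbearing potential at Visit 4 (Week 4), Visit 6 (Week 8) and Visit 8 (Week 12), done before the injection. Section 14.2 already puts all assessments ahead of dosing. State that on a positive result the dose is held and the result confirmed before treatment is permanently discontinued.

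The cost is a schedule amendment and three test kits and urine samples per woman, at visits that already take place but where urine is not now collected. No new visit or staff is needed. An occasional false positive will need confirmation, with a blood draw if by serum, and may cost the subject that dose.

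Optionally, add a urine test at Visit 12 (Week 26, 14.2.16), where urine is already taken. Subjects who do not enter the extension have no test after Day 98, although Section 14.1 requires contraception for 3 months after the last dose. This would help record pregnancies only; it has no bearing on the stop rule.
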